#### K-CBCL Evaluation

The K-CBCL is an evaluation tool used to verify the effects related to overall problem behavior, adaptation, and social performance. This test is a standardized checklist in which parents describe their children’s behavioral and emotional problems. It consists of two parts: the Social Ability Scale and the Syndrome and Total Problems Scale [32]. The K-CBCL consists of a 132-item questionnaire, and responses are provided on a 3-point Likert scale ranging from 0 to 2. It consists of a social competence scale, school performance scale, syndrome scale, and a total problem scale [32].

#### K-VABS-2 Analysis

The K-VABS-2 is an evaluation tool to verify the effects related to overall problem behavior, adaptation, and social performance. This test is the Korean version of the second edition of the VABS. It measures adaptive behavior, including 4 domains (communication, daily living skills, socialization, and motor function) and 11 subdomains (receptive language, expressive language, writing, individual, family, community, interpersonal relationship, play, ability to cope, and large and small muscle areas). This was evaluated by dividing the adaptation levels into 5 and maladaptation levels into 3 [33].

#### Symptom Checklist-Revision (SCL-R)

The SCL-R is a symptom checklist developed by Derogatis et al. It consists of 9 symptom dimensions (somatization, obsessive-compulsive disorder, interpersonal sensitivity, depression, anxiety, hostility, phobic anxiety, paranoid ideation, psychoticism, and additional items) with a total of 90 items [34].

#### CDI Evaluation

The CDI is an evaluation tool to verify the effect of improving mental health, such as relieving stress and reducing depression in children. This test measures the degree of depression in children. It is a modified version of the Adult Beck Depression Inventory (BDI) for children aged 8-13 years [35]. It consists of 27 items. The evaluation is provided in a self-report format, where the mood state of the individual is indicated in 1 of the 3 sentences describing each question [36].

#### RCMAS Evaluation

The RCMAS is an evaluation tool for testing mental health–enhancing effects, such as stress relief and anxiety. This tool is a children's version of Taylor's Manifest Anxiety Scale for Adults, and it is the most widely used self-report scale for the assessment of anxiety disorders in children and adolescents aged 0-19 years [37]. It is designed to evaluate various symptoms related to anxiety, and all 37 questions are asked to be answered with “yes” or “no” about how you think and feel about yourself.

### Recruitment

#### Ethics Approval and Consent to Participate

This study was approved by the Korea National Institute for Bioethics Policy (KONIBP), a Public Institutional Review Board (P01-202202-01-017). Before participating in the study, consent will be obtained from parents and participants (children).

### Participants

#### Setting

The intervention will be administered remotely from a treatment center for developing the social abilities of children with ASD in Korea or by self-referral through community web pages on the internet for parents with ASD.

#### Screening and Inclusion Criteria

We will recruit 24 children between March 2022 through treatment centers or internet-based social networking services. Inclusion criteria for children are the following: (1) age between 7 and 12 years, (2) diagnosed with ASD, (3) sufficient cognitive abilities to understand the rules with IQ≥90 according to a standardized intelligence test, (4) children and parents fluent in Korean, and (5) no defects in motor function. Written informed consent will be obtained from all the children and parents who will participate in this study.

#### Exclusion Criteria

Children will be excluded from the study if they do not speak, hear, or have impaired vision; if they have been diagnosed with a history of congenital or acquired brain damage, such as cerebral palsy; or if they have difficulty in cooperating with program participants because of serious developmental delays or difficulties in controlling behavior.

#### Sample Size

The sample size calculation provided by the clinical trial pilot test was employed because no studies were undertaken in advance to determine the effectiveness of the peer program by conducting exploratory clinical trials [38]. The recommended sample size for such pilot studies is 12 persons per group.

#### Randomization and Masking

Participants will be assigned (1:1) to either the experimental or control group using permuted blocks (block size 4) and stratified by age (children aged 7-9 years and 10-12 years). An independent statistician will build the randomization list with consecutive subject numbers using the PROC PLAN method in SAS version 9.4.

Researchers providing the interventions are not blind; however, those who perform the neuropsychological assessments of the participants are blinded. Because all participants will receive the same outcome measures, assessors will not be able to identify which group a participant belongs to, based on the results. Wherever possible, if an assessor becomes unblinded, further evaluations for that participant will be completed by a different assessor (blind to the arm allocation).

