
#### Neuropsychological Test

To confirm that the children who wished to participate in the study meet the research criteria, the K-WISC-IV test, an intelligence test that comprehensively evaluates the overall intellectual ability of children, will be performed before the start of the study [27]. To compare and evaluate the effectiveness of the metaverse-based social skills training program developed in this study, a series of neuropsychological tests will be performed before and after the study to evaluate sociability. Neuropsychological tests to be used in the study include the Social Responsiveness Scale (SRS), evaluated by parents, as a tool to verify the effectiveness of children's social interactions. Furthermore, the Korean version of the Child Behavior Checklist (K-CBCL) and the Korean version of the Vineland Adaptive Behavior Scale-2 (K-VABS-2) test are used as evaluation tools to verify the children's overall problematic behavior, adaptability, and sociability-related effects as determined through a parental survey. The Children’s Depression Inventory (CDI) and revised Children’s Manifest Anxiety Scale (RCMAS) are used as assessment tools to compare mental health levels, such as stress relief, depression, and anxiety before and after intervention.

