#### Intervention Group Receiving the Metaverse-Based Social Skills Training Program

The intervention group will receive the metaverse-based social skills training program developed by the researchers for 60 minutes per session once a week for 4 weeks. The program consists of direct instruction (rules for being a good sportsman) and practical training (playing sport games). Table 1 summarizes the metaverse-based social skills training program content. When the program is applied to metaverse, a wearable device will collect the child's biometric information in real time. In addition to internet-based and offline recording modes, the children's actions will be recorded using a webcam during the program.

**Table 1 table1:** Contents of the metaverse-based social skills training program.

Week	Session	Goal	Content
1	Introduction and preneuropsychological test (offline)	Orient the participants to the program	Explaining the process involved in the program and the basic rules and the use of the wearable device Preneuropsychological evaluation
2	Being a Good Sportsman 1(internet): awareness of the need for rules and results	Learn and develop the right behavior for replacing inappropriate behavior; avoid uncontrolled negative behavior to achieve positive behavior	Subject and modulator introducing themselves to each other Self-introduction by team Forming rules Playing sports games in metaverse Giving session feedback and homework
3	Being a Good Sportsman 2 (internet): understanding the situation and participating in team activities	Learn social understanding by noticing situations and conflicts that occur during team activities	Greeting therapists and participants Checking the homework from the last session Reminding rules Playing sports games in metaverse Giving session feedback and homework
4	Being a Good Sportsman 3 (internet): responding appropriately to negative behavior experiences and negative emotions	Learn to accept the result of rule violations, failures, etc experienced in team activities and understand appropriate emotional response	Greeting therapists and participants Checking the homework from the last session Educating and practicing negative emotion acceptance and coping skills Playing sports games in metaverse Giving session feedback and homework

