### Control Group

The control group will not intervene. Only neuropsychological tests will be conducted between the first and last week.

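### The blinding described covers the staff who run the assessments, but six of the seven posttest instruments are rated by parents or children who know the arm, and the timing of the baseline ratings relative to allocation is unclear.

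*Protocol article*

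**What the plan says.** Under Randomization and Masking, the protocol article states: "Researchers providing the interventions are not blind; however, those who perform the neuropsychological assessments of the participants are blinded". The reason given is: "Because all participants will receive the same outcome measures, assessors will not be able to identify which group a participant belongs to"; that sentence goes on to limit itself to what the results reveal. If an assessor becomes unblinded, a different blinded assessor takes over where possible.

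The section Neuropsychological Test says who supplies the ratings: "Neuropsychological tests to be used in the study include the Social Responsiveness Scale (SRS), evaluated by parents". It describes the K-CBCL and K-VABS-2 as covering problem behavior, adaptability and "sociability-related effects as determined through a parental survey". The K-SCQ section has the parent or primary caregiver answering. For the CDI, "The evaluation is provided in a self-report format", and the RCMAS section also calls that scale a self-report.

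On the comparator, the section Control Group says: "The control group will not intervene. Only neuropsychological tests will be conducted between the first and last week".

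On timing, the Study Design summary places random assignment after neuropsychological evaluation. Table 1 labels week 1 "Introduction and preneuropsychological test (offline)", a session that also orients participants to the program and explains the wearable device.

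**The concern.** Assessor blinding protects an outcome only if the blinded person makes the judgment that becomes the score. Here the judgments on most of the battery come from parents and children, who know whether the child attended four weekly sessions or received nothing. A parent who hopes the program helped may rate the child more favorably at posttest, and that shift adds directly to the between-group difference.

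At stake is what the trial may claim. The Study Design summary says effectiveness will be verified from within-group changes and between-group differences on these tests. A reader of the masking section would take those differences as blinded evidence. The Limitations section names technical problems, small numbers and the absence of long-term follow-up, but not rater expectancy.

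A second, smaller question is whether the baseline ratings could also be made with knowledge of the arm.

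**Working it through.** **Step 1. Who supplies each posttest rating.** The battery is the week 6 list in Table 1.

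| Instrument | Rater | Where stated |
|---|---|---|
| K-SCQ | Parent or primary caregiver | K-SCQ section |
| SRS-2 | Parent | Neuropsychological Test |
| K-CBCL | Parent | Neuropsychological Test |
| K-VABS-2 | Parent | Neuropsychological Test |
| SCL-R | Not stated | – |
| CDI | Child | CDI Evaluation |
| RCMAS | Child | RCMAS Evaluation |

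Six of seven are parent, caregiver or child ratings. The SRS-2 section says that parents or teachers can complete the scale, but that describes the instrument; for this study the text fixes "Social Responsiveness Scale (SRS), evaluated by parents". The one test described as administered by a psychologist, the K-WISC-IV, serves eligibility and baseline and is not in the posttest list.

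**Step 2. What these raters know.** Treated children attend four weekly 60-minute sessions, with homework after the first three. Controls have tests only. Parents and children both consent. The article does not say that they are unblinded, but this follows from a no-intervention comparison.

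**Step 3. What the stated safeguards cover.** Using the same measures in both arms limits what staff can infer from results. Replacing an unblinded assessor keeps staff blind. Neither changes what a parent or child knows when answering.

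**Step 4. Baseline timing.** The Study Design summary puts neuropsychological evaluation before random assignment, and it mentions the K-WISC-IV just before. That evaluation could therefore mean the screening test alone or the whole pretest battery. Table 1 puts the outcome pretest in week 1, in the program's introduction session. The Control Group section also has controls tested from the first week, and Table 1 gives no randomization date. The text permits baseline rating before or after allocation is known.

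**Step 5. Illustration of size.** No figure in the plan is at issue, so there is nothing to reproduce. Inputs from the document: n = 12 per arm (Sample Size) and significance level 0.05 (Statistical Analysis), taken as two-sided, which the text does not state. Assumptions: no true effect, a posttest rating bias b of 0.3 or 0.4 SD favoring treatment, and a pre-post correlation r.

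With 22 degrees of freedom the critical t is 2.074. The rejection probability comes from the noncentral t distribution with noncentrality d × √(n/2) = d × √6 = d × 2.449.

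- Posttest t test: d = b. For b = 0.3, noncentrality 0.735 and rejection 10.8%. For b = 0.4, 0.980 and 15.5%.
- Planned group × time ANOVA, which for two time points is equivalent to a t test on change: d = b / √(2(1 − r)), with the bias entering at posttest only.
  - r = 0.7: √0.6 = 0.775, so d = 0.387 and 0.516; rejection 14.8% and 22.7%.
  - r = 0.3: √1.4 = 1.183, so d = 0.254 and 0.338; rejection 9.1% and 12.4%.

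The nominal rate is 5% in every case.

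**The case against.** The strongest reply is that the masking section is literally true. It says that those performing the assessments are blinded and never says that parents or children are; its supporting sentence is confined to inference from results. Unblinded raters are unavoidable when a behavioral program is compared with nothing, and this is a pilot of 12 per arm that already disclaims generalization. That stands as far as it goes: the design need not be abandoned. But the disclaimer rests on sample size, not on rater bias, and blinding of administrators is the only blinding the article offers for its outcomes.

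Two stronger readings are tempting and not supported. A reader might infer from Table 1 that baseline ratings are made after allocation. The text does not show this: the design summary puts neuropsychological evaluation first, controls are tested in the first week too, and assignment for 4 weeks fits the four sessions in weeks 2 to 5. Nor is it clear that such ratings would inflate the effect, since equal bias in the same direction at both times would cancel in the change contrast. A reader might also infer that blinded staff contribute nothing to any outcome. The article does not say who scores the forms, leaves the SCL-R rater unstated, and lists wearable data as a further source for judging effectiveness.

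The illustration is open to the fair objection that the bias and correlation are assumed. The finding does not depend on them.

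**Conclusion.** The point holds. For six of seven posttest instruments the stated blinding does not reach the person making the rating, and that person knows the arm. A difference on these scales against no intervention mixes any program effect with expectancy, so it cannot alone verify the metaverse content. The conclusion rests on the article's own description of the raters and the comparator, plus the inference that families know whether they received the program.

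The size cannot be fixed from the documents. Under the assumed bias of 0.3 to 0.4 SD, the planned contrast would show a false-positive rate of about 9% to 23% across correlations of 0.3 to 0.7, against a nominal 5%.

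Baseline timing is an ambiguity to resolve, not a demonstrated error.

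**What to change.** 1. In Randomization and Masking, limit the claim to test administrators and add a sentence such as: *Parents and children, who supply the ratings, are not blinded to allocation.* State who rates the SCL-R.
2. In the conclusions and Limitations, state that differences on parent-rated and self-rated scales versus no intervention include expectancy effects and cannot be attributed to the metaverse content alone.
3. Reconcile Table 1 with the Study Design summary by stating that all baseline questionnaires, in both arms, are completed before allocation is disclosed.

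The first two are wording only. The third is wording if that order is already intended, and otherwise a change in visit order; none needs more participants. A teacher-rated SRS-2, from teachers not told the allocation, could be added as supportive evidence at the cost of one extra questionnaire per child per time point and some nonreturn. It is optional and not part of the required change.

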### Data Management

The data acquired in this study will not be viewed or leaked by anyone other than the researcher responsible for the participants’ safety, and participants’ data will be entered into the system when entering computerized data with security functions and kept confidential. Except for the information supplied by research institutes, data entered into the computerized data input system are inaccessible and are not accessed or leaked to anyone other than researchers licensed as accountable researchers. Furthermore, all research-related records will be kept for 3 years from the end of the study, per Article 15 of the Bioethics Act Enforcement Rules, and data relating to personal information among documents passed by the storage agency will be destroyed per Article 16 of the Personal Information Protection Act Enforcement Decree.

### Statistical Analysis

All baseline variables will be summarized in a randomized group. Continuous data will be reported as means (SD) unless skewed and will be reported as medians (IQR). Before testing the effectiveness of the program, an independent sample *t* test and a Mann-Whitney U test will be performed to determine whether there are differences in demographic variables between the groups. To compare the effects of all outcomes, the analysis will be conducted using the paired *t* test and Wilcoxon signed rank test. To evaluate treatment effects in each group, ANOVA will be repeatedly performed for determining differences in variables between the baseline and posttest for the treatment and control groups, with a condition analysis using (treatment vs control) × time (baseline vs posttest). ANOVA will be performed to compare the effects of the program between the groups and to determine whether there is a significant difference between each group by judging the rejection range based on a significance level of 0.05. We plan to perform statistical analysis using Python (version 3.8.5) and R (version 4.0.4).

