## Methods

### Study Design

#### Summary

This study is a parallel randomized controlled study (trial registration: KCT0006859) involving children aged 7-12 years diagnosed with ASD who volunteered to participate in the study with the consent of a legal guardian. The study will include an intervention group and a control group at a 1:1 ratio. Participants will be publicly recruited through the internet to enroll in a clinical trial through the Korean-Wechsler Intelligence Scale for Children-IV (K-WISC-IV) test administered by a professional clinical psychologist. Following neuropsychological evaluation, the children eligible for this study will be assigned randomly to the intervention or the control group for 4 weeks. Randomization will be performed using the PROC PLAN method in the SAS software program (version 9.4, SAS Institute). In this study, we plan to develop and apply a social skills training program for children with high-function ASD that can be implemented within the metaverse platform based on the PEERS program using digital technology. The PEERS is a social skills training program developed for children with ASD who face difficulties in making or retaining friends. The PEERS program has 14 sessions. The 1st session gives the introduction and trading information; the 2nd session is about conversational skills; the 3rd session is on electronic communication; the 4th session is about choosing appropriate friends; the 5th session is regarding the appropriate use of humor; the 6th session is about peer entry strategies; the 7th session is regarding peer exit strategies; the 8th session is about get togethers, the 9th is on good sportsmanship; the 10th is about handling teasing; the 11th is on handling bullying and bad reputations; the 12th is regarding arguments and disagreements; the 13th is about handling rumors and gossip; and the 14th one includes a graduation party and ceremony [12]. Under the guidance of a clinical psychologist (with a PhD in education) and a clinical specialist in psychiatry, “Becoming a Good Sportsman,” which is part of the PEERS program, was selected and conducted as a proof-of-concept study. Socializing with peers is important for children and adolescents with ASD to build close friendships and engage in positive peer interactions. To reduce the burden of discussing a wide range of topics, it is better to proceed with activities that go well together. “Becoming a Good Sportsman” was selected because experts considered it suitable for a test study because it is composed of activity-based socializing to become a good sportsman, which corresponds to the ninth session selected in our study [26]. To maintain the consistency of the program, a professional clinical psychologist trained during the study period will conduct it. To verify the effectiveness of the program, the results of neuropsychological evaluation, including social development indicators and biometric information (heart rate, heart rate variability, saturation, respiratory rate, and stress index), will be collected through wearable devices. Children enrolled in the study will be randomized into 2 groups with the same baseline characteristics. To verify the effectiveness of the program, for each group, first the differences between the neuropsychological evaluation results, including the social development index determined before the experiment and the test results after the experiment, will be compared and analyzed using a statistical method. Second, the differences in the neurophysiological scores between the groups will be compared and analyzed. Based on the results of these 2 processes, the effectiveness of the metaverse-based social skills training program using digital technology will be verified.

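### Within-arm before-after tests count as one of two bases for verifying effectiveness, and the protocol does not say that the between-group contrast decides

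*Protocol article*

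**What the plan says.** The Summary under Study Design describes a parallel randomized trial: "The study will include an intervention group and a control group at a 1:1 ratio". It then gives two steps for verifying the program. The first is taken separately in each arm and compares results before and after the experiment: "for each group, first the differences between the neuropsychological evaluation results, including the social development index determined before the experiment". The second is between arms: "Second, the differences in the neurophysiological scores between the groups will be compared and analyzed". The conclusion draws on both: "Based on the results of these 2 processes, the effectiveness of the metaverse-based social skills training program using digital technology will be verified".

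The Statistical Analysis section turns this into tests. For outcomes in general it says "To compare the effects of all outcomes, the analysis will be conducted using the paired" t test and the Wilcoxon signed rank test. The next sentence begins "To evaluate treatment effects in each group, ANOVA will be repeatedly performed for determining differences in variables between the baseline and posttest" and goes on to specify a condition-by-time analysis, "treatment vs control) × time (baseline vs posttest". A further ANOVA compares the program's effects between the groups, and the 0.05 significance level is stated for that one.

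Neither section calls the within-arm results descriptive, says that the between-group result decides, or says whether one process is enough or both are needed.

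**The concern.** A paired test inside one arm asks whether scores changed over time. It does not ask whether the program changed them. The untreated control arm, which according to the Control Group section is only tested, is there to show how much scores move anyway. A within-arm test ignores that information. A significant change in the treatment arm beside a non-significant one in the control arm is not a test of the difference between arms either.

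Shared change is plausible here. The battery is repeated after a few weeks, the children are developing, and families volunteer or self-refer. If such change may count toward verifying effectiveness, the trial could report a program effect that its own control arm does not support. With 12 children per arm and a between-group test of limited power, a favorable within-arm P value could end up carrying the report.

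**Working it through.** **Inputs from the protocol.** The Sample Size section gives 12 per group; 2 × 12 = 24 agrees with Screening and Inclusion Criteria. That size is a pilot recommendation with no effect size, SD or power behind it, so there is no calculation to reproduce. The level is 0.05, stated for the between-group ANOVA. I apply it, two-sided, to the paired tests as well, which is an assumption.

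**Assumptions.** The true program effect is zero. Both arms share the same mean improvement (drift), in units of the cross-sectional SD of the outcome. The pre-post correlation r is varied. The protocol gives neither drift nor r. Scores are taken as normal.

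**Step 1: which comparison the paired tests make.** Paired tests cannot compare two independent arms. Together with the Summary's wording about each group, they must be before-after tests within an arm.

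**Step 2: treatment-arm paired t test under no program effect.** The SD of change is √(2(1 − r)) cross-sectional SDs, so the standardized change is dz = drift / √(2(1 − r)). The rejection probability comes from the noncentral t distribution with 11 degrees of freedom and noncentrality dz × √12. With P that probability, the pattern of treatment significant and control not significant has probability P × (1 − P), because the arms are independent.

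| Drift | r | dz | P, treatment-arm test | P × (1 − P) |
|---|---|---|---|---|
| 0.3 | 0.3 | 0.3/1.183 = 0.25 | 12.7% | 0.127 × 0.873 = 11.1% |
| 0.3 | 0.5 | 0.3/1.000 = 0.30 | 15.8% | 0.158 × 0.842 = 13.3% |
| 0.3 | 0.7 | 0.3/0.775 = 0.39 | 23.2% | 0.232 × 0.768 = 17.8% |
| 0.3 | 0.9 | 0.3/0.447 = 0.67 | 56% | 0.56 × 0.44 = 25% |
| 0.5 | 0.5 | 0.5/1.000 = 0.50 | 35.3% | 0.353 × 0.647 = 22.8% |
| 0.5 | 0.7 | 0.5/0.775 = 0.65 | 53.2% | 0.532 × 0.468 = 24.9% |

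With a drift of only 0.1 and r = 0.7, P is 6.9%. By simulation, the Wilcoxon signed rank test behaves similarly: about 13% at dz = 0.3 and 31% at dz = 0.5.

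**Step 3: the planned between-arm contrast.** With two time points, the group × time interaction is equivalent to a two-sample t test on change scores. Shared drift cancels. Simulation gives 4.9% to 5.0% for dz from 0 to 0.8.

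**Step 4: the possible decision rules, by simulation with no program effect.**

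- *Either result is enough:* about 8% at dz = 0, 19% at dz = 0.3 and 38% at dz = 0.5.
- *Both results are required:* 1.6% at dz = 0, 2.3% at dz = 0.39 and 2.7% at dz = 0.65. False positives fall below 5%, but the paired test is then a hurdle unrelated to the program's effect. If untreated children worsen and treated children hold steady, the program works, yet the treatment-arm paired test has nothing to detect.

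**The case against.** The strongest reply is that the right test is already planned. The Statistical Analysis section contains the group × time analysis and a between-group ANOVA, and the only stated significance level belongs to the latter. This stands. A reader might infer that the paired tests are the sole analysis, or that randomization gives no protection at all; the text supports neither. Nor should the phrase about treatment effects in each group bear much weight, because that same sentence specifies the treatment-versus-control by time analysis.

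Second, basing the conclusion on two processes may mean both together. That reading is open, and under it false positives are not inflated (step 4). The inflated figures apply only if the within-arm result is sufficient, and the protocol states neither rule.

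Third, the size depends on inputs that the protocol does not supply. It is small for small drift and ranges from 13% to 56% at one drift value as r varies.

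Fourth, not every source of change fits. Entry is not based on a cut-off on an outcome scale, so regression to the mean is possible but not shown. Parental expectancy falls mainly on the treated arm: parents complete the Social Responsiveness Scale, and the control is untreated. A between-group contrast would not remove that bias.

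Finally, this is a proof-of-concept study whose Limitations section disclaims generalization. That lowers the stakes, but the Summary still undertakes to verify effectiveness.

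**Conclusion.** The point holds as a flaw in the stated basis for the conclusion. It is not that a valid test is absent. Within-arm change is allowed to count as evidence of effectiveness, and the rule for combining it with the between-group result is missing.

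If the within-arm result suffices, an assumed shared improvement of 0.3 cross-sectional SD gives a treatment-arm false-positive rate of about 13% to 56% for r between 0.3 and 0.9, against about 5% for the between-arm test of change. If both are required, error is not inflated, but the within-arm test adds no valid evidence and can block a real effect. Both readings need the same correction. The percentages rest on assumed drift, correlation, normality and a two-sided 0.05 level. The logical point does not depend on them.

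**What to change.** In the Study Design summary, replace the two-process rule with a statement that effectiveness is judged only from the randomized between-group contrast that uses baseline. In Statistical Analysis, name that contrast: either the group × time interaction already planned, or an ANCOVA of the posttest adjusted for baseline and the age stratum, reported with a confidence interval. Say in both places that within-arm change is descriptive and is not a test of effectiveness, and stop presenting the paired t and Wilcoxon signed rank tests as the analysis of effects for all outcomes.

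The cost is wording only, with no new data or participants. The price is that within-arm P values can no longer support the conclusion. The change does not deal with bias from parents rating outcomes while aware of allocation, which should be acknowledged separately.
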